##### Mass Treatment

All village residents will be treated with Pzq as per the treatment regime outlined below.

Stool samples will be taken from sentinel cohort members 1 month after the treatment to determine the efficacy of treatment. Those found to be egg positive would be retreated as per the regime. This process will be repeated until the subject is cured of infection.

All bovines within the intervention villages will be treated and cured with Pzq as per the treatment regime outlined below. Stool samples will be taken 1 month after the treatment to determine the efficacy of treatment. Those found to be egg positive would be retreated as per the regime. This process will be repeated until the animal is cured of infection.

**Stage 3:** March/April 2005 to May 2005

##### Snail survey

##### March/April 2005

Want to measure the prevalence of infection in snails and the density of infected snails per unit area. To do this we need to conduct random quadrat sampling (1000 frames) (20m2 or 50m2 depending on area)(Chinese method) of the marshland areas relevant to each village. Use GPS machine to provide a snail survey map

##### Mass Treatment

May 2005

All bovines within the intervention villages will be treated and cured with Pzq as per the treatment regime outlined below. Stool samples will be taken 1 month after the treatment to determine the efficacy of treatment. Those found to be egg positive would be retreated as per the regime. This process will be repeated until the animal is cured of infection.

**Stage 4:** October-November 2005

##### Outcome Measures

Humans:

Sentinel cohort members will receive 2 plastic containers for fecal samples. Containers will be labeled with PID, and the date of distribution. Participants will be instructed to deposit samples from their own faeces, separated by at most three days, into each container and to return the container immediately to one of several collection points, where the sample will be stored at 4 °C. Fecal samples returned later than 48 hours after defecation will not be accepted and new containers will be issued. Slide preparation (three slides per stool specimen) will occur 24 hours after receipt of stool sample using the Kato-Katz thick smear technique (Katz et al 1972). These samples will provide the outcome measures for each village 1 year after baseline. Water contact data will also be collected for that month via the completion of a questionnaire

Cohort members found to be egg positive will be treated for ethical reasons.

Water contact questionnaire survey

The questionnaire will be conducted once a year after transmission season (October-November) by trained team members, no more than 3 team members will be responsible for the survey for one village during the entire project period. The content of the water contact survey is listed in the questionnaire form. Each item must be answered with no blank.

Bovines:

A stool sample from every bovine will be collected and tested using the traditional Chinese MHT, These samples will provide the outcome measures for each village 1 year after baseline.

**Stage 5:** November 2005

##### Mass Treatment

All village residents will be treated with Pzq as per the treatment regime outlined below.

Stool samples will be taken from sentinel cohort members 1 month after the treatment to determine the efficacy of treatment. Those found to be egg positive would be retreated as per the regime. This process will be repeated until the subject is cured of infection.

All bovines within the intervention villages will be treated and cured with Pzq as per the treatment regime outlined below. Stool samples will be taken 1 month after the treatment to determine the efficacy of treatment. Those found to be egg positive would be retreated as per the regime. This process will be repeated until the animal is cured of infection.

**Stage 6:** March/April to May 2006

##### Snail survey

##### March/April 2006

Want to measure the prevalence of infection in snails and the density of infected snails per unit area. To do this we need to conduct random quadrat sampling (1000 frames) (20m2 or 50m2 depending on area)(Chinese method) of the marshland areas relevant to each village. Use GPS machine to provide a snail survey map

##### Mass Treatment

May 2006

All bovines within the intervention villages will be treated and cured with Pzq as per the treatment regime outlined below. Stool samples will be taken 1 month after the treatment to determine the efficacy of treatment. Those found to be egg positive would be retreated as per the regime. This process will be repeated until the animal is cured of infection.

**Stage 7:** October-November 2006

##### Outcome Measures

Humans:

Sentinel cohort members will receive 2 plastic containers for fecal samples. Containers will be labeled with PID, and the date of distribution. Participants will be instructed to deposit samples from their own faeces, separated by at most three days, into each container and to return the container immediately to one of several collection points, where the sample will be stored at 4 °C. Fecal samples returned later than 48 hours after defecation will not be accepted and new containers will be issued. Slide preparation (three slides per stool specimen) will occur 24 hours after receipt of stool sample using the Kato-Katz thick smear technique (Katz et al 1972). These samples will provide the outcome measures for each village 2 years after baseline. Water contact data will also be collected for that month via the completion of a questionnaire

Cohort members found to be egg positive will be treated for ethical reasons.

Water contact questionnaire survey

The questionnaire will be conducted once a year after transmission season (October-November) by trained team members, no more than 3 team members will be responsible for the survey for one village during the entire project period. The content of the water contact survey is listed in the questionnaire form. Each item must be answered with no blank.

Bovines:

A stool sample from every bovine will be collected and tested using the traditional Chinese MHT, These samples will provide the outcome measures for each village 2 years after baseline.

**Stage 8:** November 2006

##### Interim Analysis

An interim analysis of the results will be performed using Bayesian methods to determine if early termination of the project is possible.

If early termination is possible, a final analysis will be performed.

However, if termination is not possible the project will move on to stage 9.

**Stage 9:** November 2006 – October-November 2008

Stages 2-7 will be repeated.

**Stage 10:** November 2008

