# Protocol Bovine Intervention Trial

PARTICIPATING SITE(S)

National Institute of Parasitic Diseases, China, CDC

Queensland Institute of Medical Research, Australia

School of Population Health, The University of Queensland, Australia

STUDY MANAGEMENT

All questions concerning this protocol should be sent via email to [name] [contact]

SCHEMA

It has been hypothesized that bovine, especially buffalo, infections are responsible for the persistence of human schistosomiasis transmission in the lake and marshland areas of China. A TMRC/NIH-supported pilot intervention study in the Poyang Lake region in the Jiangxi Province concluded in 2003 and the results are supportive of this hypothesis. The bovine intervention trial aims to: 1) Repeat the results obtained from the TMRC/NIH-supported pilot intervention study. However on a larger and more generalizable scale

; 2) Examine the efficacy of bovine chemotherapy on human infection and reinfection rates; 3) Assess bovine chemotherapy as a plausible schistosomiasis control method;

4) Integrate the intervention into the earlier TMRC developed mathematical model. The study will be conducted over a maximum of 4 years, with an interim analysis after 2 years within pairs of villages.

TITLE: A bovine intervention trial

COUNTRY: China

DURATION TO COMPLETION: 2006-2008

DESIGN: Cluster-randomized design with a longitudinal study of a sentinel cohort

SAMPLE SIZE: A sample size consisting of at least 300 residents per village will constitute the sentinel cohort; all bovines will be sampled in all pairs of villages at baseline and in the intervention villages during the trial.

POPULATION: The population will be from the pairs of selected administrative villages in Hunan and Jiangxi provinces in P.R. China

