### 1.3 Study Design

**Cluster Randomized Design:** We will select pairs of villages from identified communities (human prevalence 10-15%; bovine prevalence 10-15%) in Jiangxi province and Hunan province, with pairs being matched as closely as possible on factors related to transmission: i.e. infection levels, transmission ecology (e.g.: water height, flooding patterns), and force of infection (e.g.: water contact patterns, buffalo: human numbers, sanitation practices, herding practices). The trial will aim to select the villages that provide closest matching in pairs. Within each pair, one village will be randomly chosen as intervention (bovines treated twice annually) and the other will be a control. Annual mass treatment of residents will be carried out in both villages. The end-point for the trial will be human infection rates. The efficacy of bovine treatment will be measured by the accumulated comparison of human infection rates across intervention and control villages, and will be reflected in the predicted percentage of human infection-years prevented by the intervention. Human infection rates will be assessed at the end of each year for 4 years.

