**Statistical Considerations**

**7.1 Outcome Measures**

The outcome measures for this study include the prevalences, infection and reinfection rates, intensities of infection and incidences. The end-point for the trial will be human infection rates. The efficacy of buffalo treatment will be measured by the accumulated comparison of human infection rates across intervention and control villages, and will be reflected in the predicted percentage of human infection-years prevented by the intervention. Human infection rates will be assessed at the end of each year for 4 years.

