**7.3 Statistical significance, Generalizability and Power**

In order for this study to yield results that are statistically significant and are able to be applied to a population (i.e. generalizable), there needs to be adequate power and a sample size providing an accurate representation of the affected community. It has been determined that for generalizability and statistical significance, a minimum of 4 village pairs is required, with a sample size of 300 per village, with a village population of approximately 1000.

The following table shows the power calculations based on the above minimum considerations. The

table also shows these powers with varying degrees of the bovine effect on the village and the

percentage of the bovines that are actually treated.

Assumptions

- Design effect is 1.5, in other words the actual sample size is reduced by a factor of 1.5 to give an effective sample size. This reduction is due to the extra similarity within clusters that means the observations cannot be treated as independent.
- Assume an attrition rate between years 1 and 2 of 20%.
- Assume that years 1 and 2 are independent for the cumulative power.
- Target (net) sample size is the number obtained in each village for testing (after excluding non-compliers).
- Use a significance level of 1% year 1 and 5% year 2.
- This study works on treating the whole village.
- Assume a village size of 1000.

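### Significance levels and power are planned for tests at Years 1 and 2, but the scheduled analyses fall at Year 2 and, if the trial continues, Year 4

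*Protocol*

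**What the plan says.** Two parts of the protocol describe the testing plan.

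- **Levels and power.** Among its assumptions, section 7.3 lists "Use a significance level of 1% year 1 and 5% year 2" and "Assume that years 1 and 2 are independent for the cumulative power". The table below them gives power for Year 1, for Year 2 and for the two together. The combined figure runs from 89.5% to 100% over nine rows.
- **Schedule of analyses.** The schema says "The study will be conducted over a maximum of 4 years, with an interim analysis after 2 years within pairs of villages". Section 3.1 places that look at Stage 8, November 2006: "An interim analysis of the results will be performed using Bayesian methods to determine if early termination of the project is possible". Two branches follow: "If early termination is possible, a final analysis will be performed", and "However, if termination is not possible the project will move on to stage 9". The second branch ends with the Stage 10 final analysis in November 2008. Infection is surveyed in autumn 2005, but neither the stages nor the timetable in section 3.2 contains an analysis at that point.

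On the measure itself, section 1.3 states "Human infection rates will be assessed at the end of each year for 4 years", and section 7.1 states "The efficacy of buffalo treatment will be measured by the accumulated comparison of human infection rates across intervention and control villages".

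**The concern.** The only significance levels in the protocol belong to Years 1 and 2. The only scheduled analyses belong to Year 2 and, if the trial goes on, Year 4. The two plans share one time point. There, one treats the look as the last test at the full 5%, and the other treats it as a Bayesian decision on whether to continue.

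Two things are at stake. The first is power: the most favourable figures in the table include the chance of success at a Year 1 test that the trial does not plan to make. The second is type I error: if 5% is used at Year 2 and the trial can still reach a further test at Year 4, the overall level depends on how the two are linked, and the protocol does not link them. A reader cannot tell which analysis is confirmatory, or at what level.

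**Working it through.** **Step 1. Reproduce the cumulative power.** Inputs are the yearly powers P1 and P2 in the section 7.3 table and the independence assumption stated there. The formula is 1 − (1 − P1)(1 − P2). For the first row, 1 − 0.733 × 0.197 = 0.856. The last column repeats the calculation with Year 1 power restated at a two-sided 5% level. For the first row, Year 1 power then rises from 26.7% to 49.8%, and 1 − 0.502 × 0.197 = 0.901.

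| Effect & coverage | Year 1 | Year 2 | By the stated rule | Printed | Year 1 restated at 5% |
|---|---|---|---|---|---|
| 60% & 70% | 26.7 | 80.3 | 85.6 | 89.5 | 90.1 |
| 60% & 80% | 38.1 | 88.7 | 93.0 | 95.7 | 95.7 |
| 60% & 90% | 51.3 | 94 | 97.1 | 98.5 | 98.4 |
| 70% & 70% | 38.2 | 90.1 | 93.9 | 96.2 | 96.3 |
| 70% & 80% | 53.3 | 95.5 | 97.9 | 98.9 | 98.9 |
| 70% & 90% | 68.6 | 98 | 99.4 | 99.8 | 99.7 |
| 80% & 70% | 50.9 | 95.7 | 97.9 | 98.9 | 98.9 |
| 80% & 80% | 68.0 | 98.4 | 99.5 | 99.8 | 99.8 |
| 80% & 90% | 82.7 | 99.4 | 99.9 | 100 | 100 |

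The printed figure is above the stated rule in every row, by 0.1 to 3.9 points. Rows 1, 2 and 4 are out by more than 2 points. With Year 1 restated at 5%, all nine rows agree within 0.6 points. The cumulative column therefore fits 5% in both years better than the stated 1% and 5%, although the document does not show how it was computed.

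**Step 2. Match the power to the schedule.** With no Year 1 analysis, the Year 1 and cumulative columns describe nothing that the trial does. What remains is the Year 2 column, 80.3% to 99.4%, and that applies only if the Year 2 decision is a 5% test.

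**Step 3. Error of the stated levels, taken as tests.** If the two tests are independent, 1 − 0.99 × 0.95 = 5.95%. If they are made on accumulating data with equal information per year, the correlation is √(1/2) = 0.707. The error is then 1 − P(|Z1| < 2.576 and |Z2| < 1.960) = 5.5%.

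**Step 4. Error with looks at Year 2 and Year 4.** The protocol gives no level for Year 4, no frequentist equivalent of the Bayesian rule and no sidedness, so all of these are assumptions. The formula is the same, with correlation √(2/4) = 0.707 in the base case. Levels are two-sided unless noted.

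| Assumption | Type I error |
|---|---|
| Year 2 stop acts as a 5% test, Year 4 at 5% | 8.3% |
| Same, one-sided | 8.0% |
| Same, 20% attrition every year (information 1.8 of 2.952 at Year 2) | 7.9% |
| Same, correlation 0.9 to 0.95 between looks | 7.0% to 6.5% |
| Same, looks independent: 1 − 0.95² | 9.75% |
| Year 2 stop as strict as 1%, Year 4 at 5% | 5.5% |

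High correlation is what strong, persistent village effects would produce. All these figures rest on normal approximations, which are rough with four pairs.

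**The case against.** The best defence is that the schedule is one coherent plan with two branches: stop at Year 2, or continue to a maximum of four years. The completion range of 2006 to 2008 in the schema fits that. Planning power at the earliest possible completion is legitimate, and if the trial stops, Year 2 is the final analysis. The 1% and 5% levels are assumptions of a power calculation, not a decision rule. The Bayesian threshold and the Year 4 level may sit in an analysis plan that is not shown.

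Most of this stands, and it limits what can be claimed. A reader might infer that the protocol carries a type I error of 8% to 9%. The documents do not support that: the figure requires the Bayesian stop to behave as a 5% test and Year 4 to be tested at 5%, and neither is stated. A reader might also count the Year 1 test towards the error of the trial as scheduled. That is not supported either, since no such test is planned; the 5.5% to 5.95% describes the levels in section 7.3 only. Nor are the stop and continue branches incompatible with each other, and the absence of a Bayesian threshold or a Year 4 level is not an error in itself.

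The defence does not remove the mismatch. Power at the earliest completion would be Year 2 power, whereas the table goes on to add a Year 1 test. A separate analysis plan could supply a threshold, but it could not make section 7.3 agree with section 3.1, and it would not repair the cumulative column.

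**Conclusion.** The concern holds as an inconsistency within the protocol. This part needs no assumption: the cumulative power of 89.5% to 100% includes a test that the schedule lacks, and in three of nine rows it differs by more than 2 points from what the protocol's own rule gives.

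The effect on type I error is conditional. Every scenario computed exceeds 5%, but the size, from about 5.5% to 9.75% with 8.3% as the base case, depends on how strict the Year 2 stop is, what level is used at Year 4, and how strongly the two looks are correlated.

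**What to change.** In the protocol:

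1. Name one primary test, on human incidence accumulated over follow-up.
2. Remove the Year 1 level, and with it the Year 1 and cumulative power columns.
3. Set the Year 2 stopping rule (a posterior threshold or a nominal level) and the Year 4 level together, so that the overall type I error is 5%, and state whether it is one- or two-sided.
4. Restate power for the Year 2 and Year 4 analyses under that rule.

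The rule should be calibrated by simulating the cluster-level analysis of four pairs. On normal theory, with Year 2 at half the information, about 2.9% at each look or 1% then about 4.5% would hold 5% two-sided, but these are for orientation only. With four pairs there are 2⁴ = 16 within-pair allocations, so the smallest two-sided p-value of a randomisation test is 2/16 = 0.125, and no such boundary could be met by that test. A strict early boundary such as p < 0.005 would need |t| above about 7.5 in a paired t-test on 3 degrees of freedom.

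The cost is protocol wording and a short simulation. The downside is that stopping at Year 2 becomes harder, the final level falls slightly below 5%, and the stated power will look less favourable than the present table.

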##### Final Analysis

Final results analysis

**3.2 Study Timetable**

| **Stage 1**  **(October 2004)** | **Stage 4**  **(October 2005)** | **Stage 7**  **(October 2006)** | **Stage 9**  **(October 2007)** | **Stage 9**  **(October 2008)** |
| --- | --- | --- | --- | --- |
| **Stage 2**  **(November 2004)** | **Stage 5**  **(November 2005)** | **Stage 8**  **Or**  **Stage 9**  **(November 2006)** | **Stage 9**  **(November 2007)** | **Stage 10**  **(November 2008)** |
| **Stage 3**  **(March-May 2005)** | **Stage 6**  **(March-May 2006)** | **Stage 9**  **(March-May 2007)** | **Stage 9**  **(March-May 2008)** |  |

**4.0 Selection of Subjects**

**4.1 Village selection**

- The villages (administrative and/or natural) identified, from which the study villages will be selected from need to exhibit similar characteristics; in particular:
  - The prevalence and intensity of infection at baseline within humans and bovines (particularly Buffalo). Human prevalence 10-15% and bovine prevalence 10-15%.
  - Similar transmission factors (i.e. transmission ecology and force of infection)
  - Sufficient populations of humans and bovines in order to obtain a successful and conclusive study. Approximate numbers of humans and bovines would be 1000 and 100 respectively.
  - These identified villages must be separate from any other studies (e.g. the TMRC 2 study)
  - Ideally the identified villages will be from the lake and marshland districts of the provinces Hunan and Jiangxi.
  - Bovines are separate from other villages
  - The villages are sufficiently isolated from one another
  - Village will not be relocating in the next 4 years.
- From the identified villages pairs will be selected from Hunan province and from Jiangxi province.
- Each pair will be matched as closely as possible on the following characteristics.

###### Essential

- - The matched pairs are from the same province (i.e. 2 matched pairs from Hunan, 2 matched pairs from Jiangxi).
  - The human to bovine ratio is similar within the pair.
  - The prevalence and intensity of infection at baseline within humans and bovines (particularly Buffalo) are similar.
  - The ecology of the villages must be similar (e.g. climate, water height, flooding patterns (rainfall), vicinity to lakes and/or marshlands).
  - Grazing of the bovines is within their village.
  - The villages are sufficiently isolated from one another.
  - Water contact patterns are similar.
  - No boat harbors within the village, where fishing boats frequently visit leading to the contamination of marshland by defecation of infected fishermen.

Desirable

- - Village layout and geographical size are similar.
  - Occupations of residents are similar.
  - Sanitation practices are similar.
  - Herding practices are similar.

### 4.2 Cohort Selection

# Cohort Inclusion Criteria

1. Resident of the administrative village and/or natural village selected for study.
2. Has been a resident of the village for >12 months.
3. 5-60 years of age.
4. Will not be migrating in the next 4 years.
5. Those who continuously reside in the study area over the study period*.
6. The resident has given informed consent.
7. Minors have the informed consent of their parent/guardian.

* Residents who are in the study area only weekends or once a month (such as students) are assumed not to have the same kind or an equal amount of exposure as individuals continuously resident in the study area. Inclusion of such individuals would contribute to either an overestimation or underestimation of prevalence.

Out-migration (dates and reasons) will be recorded for cohort members. Owing to the close familial relationships within the village, reporting of out-migrants will rely on family members or neighbours.

In addition, in-migrants to the area, intending to become longer-term residents will be documented, but not included in the cohort. Thus, the study will have documentation of the village population, within which the cohort is embedded.

NOTE: The sentinel cohort in each village must have at least 300 members

1. **Clinical Considerations**

